## Data Management

*Item 19: Plans for data entry, coding, security, and storage, including any related processes to promote data quality (e.g., double data entry; range checks for data values). Reference to where details of data management procedures can be found, if not in the protocol.*

**Data Entry.** Participant records are created in REDCap by Tue-MAand include pseudonym, e-mail address, study center, metadata and assessment dates. Patient records further include diagnostics and exercise therapist records include dropout-dates as well as dropout-reasons.

The data that participants enter in the smartphone application during their participation in the trial are securely stored on their phones. The data are also transmitted to a central server located at University of Tuebingen. Participants are able to share some or all of their data (that is directly related to their participation such as exercise schedules or plans for goal achievement) with their exercise therapist. They can access a summary of the participant’s data via a browser-based application in order to plan their group session or provide feedback and guidance to the individuals.

Randomization by LMU personnel is automatically triggered 2 weeks after Pre-assessment. Participants enter all questionnaire data electronically via REDCap from a date-triggered REDCap invitation link. AE and Dropout-data are entered by staff of the sponsor after notification from the therapist or the participant.

**Data Quality**. Data quality is ensured through several mechanisms: Validity, data and range rules are installed for data entry in REDCap wherever possible. All manual modification and changes to the database will be documented in electronic logs in REDCap and only e-mail addresses will be deleted from logs after data collection. Participants have to confirm it to be an intentional choice if they leave items unanswered on questionnaires. Automatic date-triggered reminders are sent to participants for questionnaires. Tue-MA receive date-triggered alerts for phone-reminders if questionnaires are still missing. Additionally, regular checks by the evaluating center help detect and prevent data discrepancies. The evaluating center will regularly send reports about missing data to the University of Tuebingen.

The trust center ensures the data quality of the routine data used for the economic evaluation by controlling for completeness of the dataset and plausibility of selected variables by calculating means and distributions.

The data transmitted from the smartphone of the participants to the server are stored in a database. New records are appended to the database and do not overwrite previous records. Faulty records can thus be interpolated with the previous and the next one. Established technical measures prevent corruption of data during transmission.

**Data Security.** A data protection concept was developed together with all partners, which was approved by the data protection officers of the University of Tuebingen, the LMU, TU and from the 2 health insurances AOK and TK. The concept can be provided upon request in German language. Violations of data privacy will be documented and reported to an external data protection officer.

The participant’s data are automatically deleted upon deletion of the study smartphone application. Transport to the server is protected by established encryption protocols. Access to the server site is protected via technical and organizational measures of the University of Tuebingen. Access to the data is only granted to specific personell responsible for technical maintenance.

All study personnel are restricted to their user rights to the necessary tasks only, i.e. LMU quality control team cannot access participants’ e-mail address while Tuebingen personnel don’t have access to participants’ questionnaire data. REDCap communication channels are encrypted, and all REDCap Data is stored on a secured internal server with logging and regular backups, which is maintained by the faculty’s IT. REDCap itself is regularly updated.

Original paper versions are safely stored in Tuebingen for 10 years after the completion of the study.

Data to and from the trust center will be transmitted via a secure online connection. Only pseudonymous data is transmitted. For data quality checks the data will be stored and analyzed on an external server without any network connections. Thereafter, data will be locked on an external hard drive within a Veracrypt container and kept within a steel safe. Data is permanently erased one year after the completion of the study.

## Statistical Methods

*Item 20a: Statistical methods for analyzing primary and secondary outcomes. Reference to where other details of the statistical analysis plan can be found, if not in the protocol.*

*Item 20b: Methods for any additional analyses (e.g., subgroup and adjusted analyses).*

*Item 20c: Definition of analysis population relating to protocol non-adherence (e.g., as randomised analysis), and any statistical methods to handle missing data (e.g., multiple imputation).*

To test Hypotheses 1, 2, 3a and 4 we will use multilevel modeling to establish the treatment effects on the primary outcome (global symptom severity) and the secondary outcomes (major depressive disorders, insomnia, panic disorder, agoraphobia, PTSD, QALYs, exercise). In these analyses, each outcome will be predicted by the group (ImPuls + TAU vs. TAU), time (pre vs. post vs. follow-up), and their interaction. Given that the randomization is stratified by study site, we will account for the effects of study site in all analyses. All analyses will be performed on intention-to-treatment basis, using maximum likelihood estimations.

To test Hypothesis 3b, mediation analyses will be performed to test the indirect effects of the treatment on the primary outcome that are mediated by the changes in the putative mediators (self-reported exercise in minutes per week, accelerometry-based moderate to vigorous physical activity (MVPA); from pre to post, pre to follow-up and post to follow-up). We will compute standardized change scores for the outcome and mediators (Lee et al., 2019). In a path model (specified in the framework of structural equation modeling), the group variable predicts the changes in the mediators, and these mediating factors further predict the change score in the outcome. The indirect effects are defined by the products of the group-mediator and mediator-outcome effects. As exploratory analyses, we will also examine other forms of mediations proposed by Goldsmith et al. (Goldsmith et al., 2018), encompassing cross-lagged effects and latent change score models. As recommended by Usami et al.(Usami et al., 2019), we will first test whether these models fit the data well (and which model fits the data best), and then investigate the indirect effects of the treatment on the outcome.

To further analyze clinical significant changes (additional analysis for Hypothesis 4 and 5), the Reliable Change Index (RCI) (Balkin & Lenz, 2021; Jacobson & Truax, 1992; Zahra, 2010) will be computed for each individual between pre-, post and follow-up assessments. Jacobson and Truax suggest combining the RCI with an estimation of a cut-off point between a functional (nonpatient) and dysfunctional (patient) population, describing a clinically significant change (Jacobson et al., 1984; Jacobson & Truax, 1992). We will check if individual scores are more than 2 SD away from the mean of the complete sample. Each individual will be classified into one of four categories: recovered (individual has passed cut-off point of clinically significant change and the RCI is greater than 1.96), improved (individual has not passed cut-off point but the RCI is greater than 1.96), unchanged (individual has not passed neither cut-off point nor is the RCI greater than 1.96), or deteriorated (the individual’s RCI is greater than -1.96). Non-parametric generalized mixed models will be conducted to analyze differences between intervention and control group.

Concerning process evaluation:

Empowerment of exercise therapists (research question 1a) will be analyzed descriptively (mean, standard deviation) with respect to their self-reports on the modified training evaluation scale (Göhner et al., 2018), the (occupational-) self-efficacy scale (Rigotti et al., 2008) and concerning the frequency of supervision.

We descriptively present the adherence score (mean, standard deviation) as well as the corresponding percentage to check whether the desired high level of adherence (>90%) in the context of the efficacy trial is achieved (research question 1b).

We descriptively present the amount of all patients acquired by each strategy as well as the amount of all patients included in the study by each strategy. We then check which recruitment strategy has the highest inclusion rate and present the corresponding percentage (research question 1c).

Referring healthcare professionals’ opinion on the new treatment option is presented descriptively (mean, standard deviation) (research question 1d).

To provide information about the dose delivered (research question 1e), we present documentation data of exercise therapists and the web-based ImPuls interface descriptively.

To assess barriers and facilitators (research question 2a), we use quantitative data from questionnaires (barriers and facilitators assessment instrument (B&F-A; Harmsen et al., 2005), satisfaction scale (Göhner et al., 2018; Johnson & Caldwell, 2011), as well as basic recommendations for outpatient facilities in Germany (Deutsche Rentenversicherung Bund (DRV), 2014; Geidl et al., 2018; GKV Spitzenverband)). Results are presented descriptively (mean, standard deviation) to provide an overview over contextual characteristics. This data is further complemented with qualitative data from the interviews.

We evaluate the interviews in a deductive-inductive process following the steps of a content-structuring qualitative content analysis (Kuckartz, 2016). First, two researchers will elaborate a preliminary coding frame for coding based on the interview guideline. Subsequently, 15% of all interviews are independently coded by those researchers. Inter-coder-reliability analysis is then performed to ensure that the elaborated coding frame is applicable. Potential discrepancies are discussed to refine the coding frame in an iterative process. This process is continued until both researchers agree that the categories are distinct and no new categories need to be added to the coding frame. Afterwards, the remaining interviews are coded. Coding and analysis are done by using the software MAXQDA 2022 (VERBI, 2021). In a final step, the statements from all interviews are summarized category by category and used to supplement the quantitative data.

We will conduct mediation and moderation analyses as well as subgroup analyses to gain deeper insight into the impact of the program (mechanisms of change). We check whether exercise therapists’ attitude towards mental disorders (Opening minds scale for health-care providers (OMS-HC; Modgill et al., 2014)), evidence-based practice (evidence-based practice attitude scale – German version (EBPAS-36D; Szota et al., 2021)) and the program ( measurement of therapy expectation and therapy evaluation of patients (PATHEV; Schulte, 2005), B&F-A) affects treatment effects (research question 3a). In addition, patients’ application data as well as changes in respective individual behavioral determinants (e.g., action and coping plans; Physical activity-related health competencies (PAHCO; Sudeck & Pfeifer, 2016)) will be used to determine the extent to which core components of the intervention have been used and how this affects treatment effects (research question 3b). Further analysis is done to determine the extent to which motivational/volitional core components of the ImPuls intervention (application data [barrier management, goal-setting], documentation data [phone contacts]) as well as changes in respective individual behavioral determinants (e.g., action and coping plans; [PAHCO]) affect patients’ exercise adherence (research question 3c). Finally, we want to explore whether psychological processes such as emotional intelligence (Trait emotional intelligence questionnaire (TEIQue; Petrides & Furnham, 2006)), emotional regulation (difficulties in emotion regulation scale (DERS; Gratz & Roemer, 2004)), repetitive negative thinking (perseverative thinking questionnaire (PTQ; Ehring et al., 2011)) or perceived stress (perceived stress scale (PSS; Schneider et al., 2020)) mediate the treatment effect on global symptom severity (research question 3d).

Missing data will be handled by multiple imputations.

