Despite the promising evidence for MVAE as an intervention for patients with mental disorders, exercise programs or professional exercise therapy are currently not provided as regular health services within the outpatient mental health care system in Germany. With the aim of combining the current evidence on the efficacy of MVAE and sustained exercise behavior change with specific demands of a real-world outpatient health care setting, ImPuls was developed as a manualized group exercise intervention (Wolf et al., 2020; Zeibig et al., 2021) for physically inactive outpatients suffering from major depressive disorders, insomnia, panic disorder with or without agoraphobia and PTSD. ImPuls integrates recent findings about the optimal modalities of exercise for therapeutic efficacy, such as optimal frequency, intensity, time/duration and type of exercise (FITT criteria) for the targeted disorders and evidence regarding sustainable behavior change by integrating behavior change techniques (BCTs). The components of this intervention are further tailored towards the specific needs of outpatients with mental disorders in the current German mental health care setting. Specific features are 1) the inclusion of a broad range of heterogenous diagnoses for which prior research has demonstrated therapeutic efficacy, 2) intervention delivery in group format, and 3) short duration (i.e., only 4 weeks of supervised MVAE sessions carried out inhouse in each study site). The aim of the current study is to investigate the efficacy and cost-effectiveness of implementing ImPuls within the outpatient mental health care setting in Baden-Württemberg, a representative state in South-West Germany. The following hypotheses will be tested:

1. Participants in the intervention condition, who have received ImPuls in addition to TAU, will show lower global symptom severity at post-treatment and follow-up assessments compared to a control condition with TAU only.

2. Overall costs in the intervention condition will represent a significant saving for the public health system compared to the control condition at post-treatment and follow-up assessments.

3a. The intervention will lead to significantly higher levels of MVAE at post-treatment and follow-up assessments compared to the control condition.

3b. The effect of condition on the reduction of the primary outcome global symptom severity will be mediated by an increase in MVAE.

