#### **Health related quality of life.** Health related quality of life will be assessed by the German version of the EQ-5D-5L questionnaire (Herdman et al., 2011; Hinz et al., 2014). It consists of five items concerning the domains mobility, self-care, usual activities, pain or discomfort and anxiety or depression with five answer alternatives each (range: 1-5). The combinations of the answer alternatives can be described with a five-digit number (i.e. the pattern 11111 indicates the optimal health state). Through the EQ-5D-5L questionnaire Quality Adjusted Life Years (QALY) are captured for the economic evaluation. The EQ-5D-5L has an internal consistency of Cronbach’s α = .86 among German chronic heart failure patients. Current data concerning internal consistency in patients with mental disorders exists for the Spanish version of the EQ-5D-5L. Among Spanish patients with major depression the EQ-5D-5L has an internal consistency of Cronbach’s α = .77 (Bilbao et al., 2021).

**Routine data of the health insurances/health care costs**. For the economic evaluation, patients’ routine data collected 6 months before the intervention, during the time of the intervention, and six months after the intervention will be provided by the two participating statutory health insurers (AOK and TK). This data will include patients’ master data, such as gender and age, as well as patient treatment costs. Parameters for treatment costs will comprise costs of inpatient and outpatient care as well as medication, medicals aids or days of incapacity to work. Routine data for each patient will be provided for the time of the intervention as well as one year prior and one year after. The relevant costs are assessed and aggregated as quantities. In addition, cost parameters resulting from the intervention and the implementation will be considered. Subsequently, routine insurance data will be linked to primary data collected.

**Change of health insurance during study participation.** In the case of a change of health insurance company during the study participation, the corresponding participant is still part of the study and continues to complete the assessments. However, routine data of the health insurances/health care costs cannot be provided.

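### Hypothesis 2 concerns costs, but the model assigned to test it lists QALYs and no cost variable, and fits QALYs at three visits, one of which can have no QALY

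*Protocol*

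**What the plan says.** In the Introduction (Item 7), Hypothesis 2 is a pure cost claim: "Overall costs in the intervention condition will represent a significant saving for the public health system compared to the control condition", to be shown at post-treatment and at follow-up.

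Under Secondary Outcomes the protocol keeps two economic variables apart. One is health-related quality of life from the EQ-5D-5L: "Through the EQ-5D-5L questionnaire Quality Adjusted Life Years (QALY) are captured for the economic evaluation". The other is health care cost from insurer routine data, with the cost of the intervention and its implementation added.

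Statistical Methods (Items 20a–c) then states: "To test Hypotheses 1, 2, 3a and 4 we will use multilevel modeling to establish the treatment effects". The outcomes are global symptom severity and "the secondary outcomes (major depressive disorders, insomnia, panic disorder, agoraphobia, PTSD, QALYs, exercise". One specification serves them all: "each outcome will be predicted by the group (ImPuls + TAU vs. TAU), time (pre vs. post vs. follow-up), and their interaction".

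The cost window is given twice in the routine-data paragraph. First it is "patients’ routine data collected 6 months before the intervention, during the time of the intervention, and six months after the intervention"; a later sentence extends the data to a full year on either side of the intervention. Data Collection Methods (Item 18b) uses six months on either side. No other section gives a model for costs.

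**The concern.** The protocol does not leave the test of Hypothesis 2 open. It names a method and a set of outcomes, and the two do not fit the hypothesis. A difference in QALYs between arms can neither confirm nor refute a cost saving. The only economic variable that is listed also cannot take the form that the model requires.

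Cost-effectiveness is a stated aim of the trial. An analysis plan that follows this passage literally has no cost outcome for Hypothesis 2 and has to put utility in place of QALYs. One that does the sensible thing departs from the protocol. The primary analysis is not affected.

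**Working it through.** The protocol gives no QALY or cost figure to reproduce. Its one computed figure, the minimum sample size of 375, plays no part here. The check compares the passages and then uses short arithmetic on assumed utilities.

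**1. Hypothesis against outcome list.**

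| Item | Variable |
|---|---|
| Hypothesis 2 (Introduction) | Overall costs |
| Secondary Outcomes | EQ-5D-5L/QALY and health care costs, as separate outcomes |
| Model for Hypothesis 2 (Statistical Methods) | QALYs listed, costs not listed |

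**2. QALYs against the time factor.** The Recruitment section places the assessments before randomisation and at 6 and 12 months after it. Let the EQ-5D-5L utilities be U0, U6 and U12. By the area under the curve, with time in years:

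- QALY for months 0–6 = 0.5 × (U0 + U6)/2
- QALY for months 6–12 = 0.5 × (U6 + U12)/2
- 12-month QALY = 0.25·U0 + 0.50·U6 + 0.25·U12

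Take assumed utilities of 0.60, 0.70 and 0.70:

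- Months 0–6: 0.5 × 1.30/2 = 0.325
- Months 6–12: 0.5 × 1.40/2 = 0.350
- Total: 0.675

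Three assessments give two interval QALYs, or one total. None belongs to the pre visit, so a three-level time factor cannot be filled with QALYs. It can be filled with U0, U6 and U12.

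Baseline utility is also part of the first interval. With U0 at 0.50 in place of 0.60, the 0–6 month QALY becomes 0.5 × 1.20/2 = 0.300. A comparison of QALYs between arms should therefore adjust for baseline utility.

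**3. Illustration of reading utility as QALYs.** Assume no difference between arms at baseline and a gain of 0.05 at both 6 and 12 months. The arm-by-time coefficient for utility is then 0.05 at each visit.

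- 12-month QALY gain: 0.50 × 0.05 + 0.25 × 0.05 = 0.0375; ratio 0.05/0.0375 = 1.33
- First six months: 0.25 × 0.05 = 0.0125; ratio 0.05/0.0125 = 4

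The two ratios are 1/0.75 and 1/0.25, so they do not depend on the value 0.05. They do depend on the gain being equal at both visits. If a gain of 0.05 at six months had vanished by 12 months, the 12-month QALY gain would be 0.50 × 0.05 = 0.025, and the six-month coefficient would overstate it 2-fold.

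**4. Costs against the time factor.** The intervention runs for 24 weeks. Six-month windows give periods of about 26, 24 and 26 weeks before, during and after it, close to equal in length. They end about 24 + 26 = 50 weeks after the start, near the 12-month follow-up. One-year windows give about 52, 24 and 52 weeks and end about 24 + 52 = 76 weeks after the start, well past that follow-up. Either version can supply a before, during and after cost, but the two define different outcomes for Hypothesis 2.

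**The case against.** Four points can be made for the protocol.

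- **The list is shorthand.** It is pooled over four hypotheses, names disorders in place of instruments and leaves out the PSQI. Costs do appear under Secondary Outcomes, so their absence from the list may be an oversight, and nothing says that QALYs are the test of Hypothesis 2. This is a fair reading, but the protocol still names no cost outcome for a hypothesis that it expressly assigns to this model.
- **QALYs may be loose wording for the EQ-5D-5L index.** The index fits the model exactly, and the design section says that all outcomes are included at every assessment. This is plausible. The text does not say so, however, and it describes QALYs as a quantity for the economic evaluation.
- **Period costs can be fitted.** Costs before, during and after the intervention could fill the three time levels, and the arm-by-time term would be a usable contrast. This stands. For costs the defect is omission and an unsettled window, not a model that cannot work.
- **A separate economic analysis is likely.** The authors' contributions assign health economics to its own team, and Item 18b describes a separate linked dataset. A health-economic plan may therefore exist. A reader might infer that Hypothesis 2 will go untested in the trial; the document does not support that.

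A reader might also infer that any cost-per-QALY result will be wrong. The protocol defines no such ratio and nowhere says that the interaction coefficient will be read as QALYs gained.

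**Conclusion.** The mismatch holds on the text. Statistical Methods assigns a cost hypothesis to a model whose list has no cost variable, and it applies a pre/post/follow-up structure to QALYs, which have no pre value. The QALY model can be run only with point-in-time utility in place of QALYs. For costs, the outcome is not named and its period is stated in two incompatible ways.

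The conclusion rests on the usual meaning of a QALY as utility accumulated over time and on the three assessment times in the protocol. The 1.33-fold and 4-fold figures illustrate a possible misreading, under a gain assumed equal at both visits; they do not measure an error in the plan. The point concerns secondary and economic outcomes only. It should be corrected in the protocol, since a later analysis plan would otherwise have to inherit the mismatch or contradict it.

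**What to change.** In Statistical Methods:

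1. Name total cost per patient, including intervention cost, over a stated accrual period as the outcome for Hypothesis 2, and state how cost in the period before the intervention is taken into account.
2. Replace QALYs in the repeated-measures list with the EQ-5D-5L index.
3. Analyse one 12-month area-under-the-curve QALY per patient, and compare the arms with adjustment for baseline utility.

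In the routine-data paragraph and Item 18b, reconcile the six-month and one-year windows so that the cost outcome has one definition. The choice of model for skewed costs can be left to the analysis plan.

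The cost is revised wording and a standard health-economic script. No new data are needed.

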4. Participants in the intervention condition will show lower disorder-specific symptoms (major depressive disorder, insomnia, panic disorder with or without agoraphobia and PTSD) compared to participants in the control condition at post-treatment and follow-up assessments

We will further assess, if participants in the intervention condition show more instances of clinically significant change compared to participants in the control condition at post-treatment and follow-up assessments (Additional analysis to Hypothesis 1 and 4)

The main objectives of our process evaluation are a) to support the findings of the ongoing pragmatic randomized controlled trial by confirming that its efficacy is truly attributable to the ImPuls intervention and b) to discover further crucial factors for the implementation of ImPuls into real-world outpatient mental health care settings.

The main research questions of the process evaluation are:

1. Implementation:
   1. To what extent did our actions empower exercise therapists (i.e., competence, acceptance) to deliver the intervention?
   2. To what extent do exercise therapists implement intervention components as intended (treatment fidelity) and what are reasons for its potential variance?
   3. Which strategies recruited the most patients and how valid were the referrals in terms of acquisition/inclusion?
   4. How do referring healthcare professionals rate the ImPuls intervention in terms of acceptability, appropriateness and feasibility?
   5. To what extent were all ImPuls sessions offered as planned and all telephone contacts made as scheduled?
2. Context:
   1. What barriers and facilitators did exercise therapists and managers experience concerning the implementation of the ImPuls intervention?
3. Mechanisms of Impact:
   1. To what extent do attitudes of exercise therapists towards the ImPuls intervention (e.g., acceptability, appropriateness) moderate the treatment effects?
   2. To what extent do patients’ integration of core components of the ImPuls intervention (e.g., amount of exercise, barrier management, goal-setting) as well as changes in respective individual behavioral determinants (e.g., action and coping plans; physical activity-related health competencies) mediate the treatment effects?

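### The clinically-significant-change rule prints the wrong bound for deteriorated and no lower bound for unchanged, so its four categories overlap and misplace reliably worse patients

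*Protocol*

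**What the plan says.** The Introduction (Item 7) announces, as an addition to Hypotheses 1 and 4, an assessment of whether intervention participants "show more instances of clinically significant change compared to participants in the control condition". This is to be examined at both later time points. Statistical Methods (Items 20a-c) gives the rule, and it asks for a single class per person: "Each individual will be classified into one of four categories". The classes are set as follows.

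- Recovered and improved share one condition, "RCI is greater than 1.96". They differ only in the cut-off, which a recovered patient has passed and an improved patient has not.
- The unchanged class is worded as "individual has not passed neither cut-off point nor is the RCI greater than 1.96", which sets no floor for the RCI.
- Deteriorated is printed as an RCI above minus 1.96, with no condition on the cut-off.

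The cut-off itself rests on this sentence, which gives no direction: "We will check if individual scores are more than 2 SD away from the mean of the complete sample". The arms are then to be compared on these categories with generalized mixed models. No other section restates or corrects the rule.

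**The concern.** Improvement sits above +1.96, so reliable worsening has to sit below -1.96. The printed inequality points the other way and takes in everyone except the reliably worse. Unchanged excludes only RCI values above 1.96, so it absorbs patients who worsened reliably without passing the cut-off.

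At stake is the categorical outcome compared between arms. Overlapping classes cannot be entered as one outcome. An analyst would have to decide, with data in hand, which label wins, and that choice determines the reported numbers of unchanged and deteriorated patients in each arm.

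**Working it through.** **Inputs.** The four definitions and the one-category requirement come from Statistical Methods. The scale direction (higher is worse) and the GSI reliability of .89 come from Primary Outcome. The protocol states no result for this rule, so there is no figure of its own to reproduce here. The threshold 1.96 is the two-sided 5% normal limit (1.95996).

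**Step 1: the printed rule, cell by cell.** This step needs no assumption.

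| Cut-off | RCI | Classes met as printed |
|---|---|---|
| passed | > 1.96 | recovered and deteriorated |
| passed | > -1.96 and ≤ 1.96 | deteriorated only |
| passed | ≤ -1.96 | none |
| not passed | > 1.96 | improved and deteriorated |
| not passed | > -1.96 and ≤ 1.96 | unchanged and deteriorated |
| not passed | ≤ -1.96 | unchanged only |

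Three of the six cells carry two labels and one carries none. No patient with RCI ≤ -1.96 is called deteriorated.

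**Step 2: share meeting deteriorated as printed.** If RCI is N(m,1), the share is P(Z > -1.96 - m).

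- m = 0: P(Z > -1.96) = 97.5%
- m = 0.5: P(Z > -2.46) = 99.3%
- m = 1: P(Z > -2.96) = 99.8%

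A simulation gave about 77% to 100%. Its inputs are assumptions that the protocol does not supply: reliability 0.80 to 0.95, mean improvement 0 to 0.7 SD, and SD of true change 0 to 0.8.

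**Step 3: the empty cell under the printed text.** This is cut-off passed with RCI ≤ -1.96. In the same simulation it held less than 0.05% of patients when the cut-off counts only towards fewer symptoms. It reached about 4.4% at most when more than 2 SD in either direction counts.

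**Step 4: correct the sign only** (deteriorated = RCI < -1.96).

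| Cut-off | RCI | Classes met |
|---|---|---|
| passed | > 1.96 | recovered |
| passed | -1.96 to 1.96 | none |
| passed | < -1.96 | deteriorated |
| not passed | > 1.96 | improved |
| not passed | -1.96 to 1.96 | unchanged |
| not passed | < -1.96 | unchanged and deteriorated |

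With no true change, the share meeting deteriorated falls from 97.5% to 2.5%. One overlap remains, and the gap moves to a fuller cell. In the simulation that cell held about 0.6% to 6% of patients (0.8% to 5.4% at reliability 0.89), depending on the assumptions and on how passing the cut-off is read.

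**Step 5: reach.** The sample size does not use this rule. With d = 0.348, two-sided 0.05 and 80% power, a t-test needs 131 per arm, or 262 in total; 262/0.70 = 374.3, which rounds up to the stated 375.

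**The case against.** The best defence is that this is a slip whose meaning can be recovered. The class is named deteriorated, the limits are symmetric, the Jacobson-Truax method is cited, and the text asks for one class per person. An analyst would probably read beyond -1.96 and would not call a recovered patient deteriorated. That is plausible, but it does not rescue the rule. Step 4 shows that the sign-corrected rule still has an overlap and a gap, and the overlap falls on exactly the reliably worse patients.

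A second defence is that the classes might be applied in the printed order, with the first match winning. The 97.5% would then not be reported: deteriorated would hold only patients past the cut-off with RCI above -1.96 and up to 1.96. This stands as a limit on the 97.5%, which is the share meeting the condition with overlaps counted. It does not help the plan. Reliably worse patients short of the cut-off would still be filed as unchanged, and the same happens in that order after a sign correction alone.

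Two stronger readings are tempting, and the protocol does not support them:

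- A reader might infer that a patient who passes the cut-off without RCI above 1.96 has no category as printed. If that patient's RCI is above -1.96, the printed text does give a category, namely deteriorated. The cell becomes a gap only once the sign is corrected.
- A reader might infer that the trial's harm signal is inverted. The Harms section lists significant worsening of pre-existing psychological symptoms as an adverse event, collects adverse events separately, and sends serious ones to the Data Safety and Monitoring Board. The RCI classes have no stated role there.

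**Conclusion.** Wrong as written, of moderate severity. The contradiction with the one-of-four requirement follows from the text alone: every recovered or improved patient also meets deteriorated, and a reliably worse patient who has not passed the cut-off meets only unchanged. The 97.5% rests on RCI being about N(0,1) with overlaps counted. In that case the 2.5% below -1.96 reflect measurement error, not true worsening. The cell without a category under the printed text is close to empty if the cut-off counts only in the healthy direction, so it is the lesser part of the problem. The simulated ranges rest on assumed inputs; the cell-by-cell check does not.

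The damage is confined to the between-arm comparison of change categories. The primary multilevel model, the sample size and the adverse event monitoring are unaffected.

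**What to change.** Replace the definitions before any unmasked analysis:

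- RCI = (earlier score - later score)/S_diff, where S_diff is the standard error of the difference, so that positive means improvement on every symptom scale.
- Recovered: RCI > 1.96 and cut-off passed.
- Improved: RCI > 1.96 and cut-off not passed.
- Unchanged: -1.96 ≤ RCI ≤ 1.96, whatever the cut-off status.
- Deteriorated: RCI < -1.96.
- The 2 SD cut-off counts only in the direction of lower symptoms.

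These classes are exclusive and exhaustive: RCI is split into three bands, and only the top band is divided by the cut-off. The same edit should correct the label in Statistical Methods that ties this analysis to Hypotheses 4 and 5, because the Introduction names Hypotheses 1 and 4 and lists no fifth. The cost is a few lines of text in the protocol or the analysis plan, with no new data and no change to the sample size.
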